## Abstract

**Background:**

Community-Based Sociotherapy (CBS) is an approach that was introduced in Rwanda in 2005, with the aim of improving psychosocial well-being among its participants and facilitating reconciliation processes. Over the years, CBS has been adapted contextually and the effectiveness of the approach has been measured in different ways, using qualitative and quantitative study designs. This study specifically assesses the effectiveness of CBS in terms of fostering the social dignity of participants as the primary outcome.

**Methods/design:**

A cluster randomized controlled trial design with person-level outcomes whereas the CBS treatment is delivered at the cluster level. A total of 1200 eligible participants will be randomly assigned to two groups in a 1:1 ratio. Participants in the intervention group will receive the CBS intervention, while the control group will be waitlisted. The primary outcome measure is a self-designed and psychometrically validated Social Dignity Scale. The secondary outcome measures will be the WHO (Five) Well-Being Index (WHO-5), the Multidimensional Scale of Perceived Social Support (MSPSS), the Posttraumatic Stress Disorder Checklist for DSM-5 (PCL-5), the Self-reporting Questionnaire (SRQ-20), and the perceived parental self-efficacy scale. The primary analysis will be performed following an intention to treat analysis, using generalized estimating equation modeling.

**Discussion:**

We expect this cluster randomized controlled trial to provide insight into the effectiveness of CBS on social dignity and secondary psychosocial outcomes among its group participants, who have different socio-historical backgrounds including genocide survivors, perpetrators, bystanders and their descendants, people in conflicts (family/community), and local leaders. This study will inform CBS implementers, policymakers, practitioners, and other stakeholders on the role of social dignity in interventions that focus on psychosocial healing.

**Trial registration:**

ISRCTN ISRCTN11199072. It was registered on 2 April 2022.

**Supplementary Information:**

The online version contains supplementary material available at 10.1186/s13063-022-06994-3.

## Introduction

The twentieth century was characterized by multiple genocidal events. This includes the genocide against the Jews, known as the Holocaust between 1941 and 1945; the Armenian genocide in 1915; the Cambodian genocide between 1975 and 1979; the genocide in the former Yugoslavia between 1992 and 1995; and the 1994 genocide against the Tutsi in Rwanda [1, 2]. Genocides leave long-lasting psychological and social harm to victims and perpetrators [3, 4]. During the 1994 genocide against the Tutsi, Rwanda was immersed in a brutal wave of organized violence in which approximately one million Rwandans lost their lives in a period of only 3 months [2, 5]. The 1994 genocide against the Tutsi in Rwanda, as opposed to other places where genocidal acts happened, has been massively executed by people known to the victims. By 1996, about 120,000 people were jailed due to genocide-related crimes (i.e., killings, rape, and destroying properties) [6], and later some of them returned to their community. After the release of prisoners, survivors had no other choice than to live alongside their perpetrators in the same neighborhood in post-genocide Rwanda.

A sizeable proportion of Rwandans were exposed to traumatic events during the genocide period resulting in a high prevalence of mental health problems [7]. Thirty-seven percent of men and 35% of women were exposed to at least one traumatic incident, such as being raped, witnessing an unnatural death, or being forced to escape their homes [7, 8]. Many Rwandans fled to neighboring countries and part of them came back a few years later [9, 10]. Consequently, mental disorders, including post-traumatic stress disorder (PTSD), depressive disorders, psychotic disorders, and substance use disorders, are the most often diagnosed disorders in the adult population in Rwanda today [11–15]. Worryingly, studies have shown that the transmission of trauma and PTSD, violence, and propensities to divisionism across generations is an issue of concern in the Rwandan community [16, 17]. In 1994, post-genocide, the entire health care infrastructure including the mental health care infrastructure was destroyed, while the needs were overwhelming. Efforts to rebuild the country led to a more stable situation. National (public and private) and international interventions addressing the negative consequences of genocide, such as trauma, impunity, a destroyed social fabric, and poverty, were implemented with notable positive gains.

The Community-Based Sociotherapy (CBS) intervention is one of the programs initiated in Rwanda to address the psychosocial needs of the Rwandan population in the aftermath of the 1994 genocide against the Tutsi and to restore the social fabric. The intervention is built on six consecutive phases, each focusing on a specific theme: safety, trust, care, respect, new life orientation, and memories. Throughout these phases, the following principles are applied: interest, equality, democracy, here and now, responsibility, participation, and learning by doing [18]. Compelling evidence shows that this psychosocial peacebuilding intervention promotes social cohesiveness, psychological well-being, reconciliation, and economic development for the study participants in Rwanda [8, 19]. CBS is also evidenced in other conflict/post-conflict settings, including in the Democratic Republic of Congo [20] and Liberia [8].

Furthermore, exploratory studies highlighted challenges related to the psychosocial reintegration of released prisoners. After their release, they usually go back to their respective families and communities, where local realities have changed. It is difficult for them to adapt to these new realities, especially when they still present feelings of worthlessness, self-stigma, and guilt. The studies mentioned above and the challenges still observed have informed the current “Mvura Nkuvure: Intergenerational healing and community reconciliation for sustainable peace” project that is being implemented by CBS Rwanda and its partners Anglican Church Byumba Diocese (EAR-D) and Prison Fellowship Rwanda (PFR) since November 2018 and Duhumurizanye Iwacu Rwanda (DIR) since December 2021.

Although CBS is a well-established intervention that can be adapted to and adopted by different contexts [8, 18], little is known about its effectiveness in increasing the social dignity of its participants. The choice for selecting “social dignity” as our primary outcome was made based on elaborate qualitative work with the CBS experts that resulted in identifying improved “social dignity” as the main outcome variable of their intervention. In a series of workshops, we explored the question of what CBS experts conceive to be the main indicators that together constitute the main outcome of the CBS intervention. We used structured equation modeling as the analytical framework to guide this exercise. This exercise led to the identification of a number of phases and principles (i.e., safety, trust, care, respect, equality, democracy) that can be understood in terms of long-term changes that CBS experts wish to see in participants after they have graduated from the intervention. Through an iterative process of literature review [21–24], interpretative work with CBS experts, and psychometric validation work on pilot data, we established an operational definition of “social dignity” within context and developed a validated questionnaire to measure the concept. We are preparing a separate publication on the contextualized conceptualization of social dignity and the development and validation of the social dignity scale [in preparation]. Improved mental health, higher levels of reconciliation, and increased social-economic wellbeing are understood as secondary outcomes to this primary outcome. We opted for a cluster design because of the nature of the CBS intervention. As CBS groups are composed of 10 to 15 people, these formed the natural clusters for our RCT study.

### Study objective

➣ To examine whether CBS enhances social dignity among its participants.➣ To evaluate whether CBS improves mental health and psychosocial well-being among its participants.➣ To investigate whether CBS’s impact on social dignity is mediated by improving mental health and psychosocial well-being.

### Study hypotheses

➣ CBS increases social dignity among its participants.➣ CBS improves mental health and psychosocial well-being among its participants.➣ CBS’s impact on social dignity is mediated by the improvement of mental health and psychosocial well-being.

### Trial design

This study will use a two-level cluster randomized controlled trial design with person-level outcomes and treatment delivered at the cluster level (the allocation fraction 1:1). One arm will serve as a control (control). At the same time, the other will receive the CBS treatment (Intervention). The design and report of this clinical trial protocol follow the Standard Protocol Items: Recommendations for Interventional Trials (SPIRIT) 2013 statement (Additional file 1), [25].

## Methods

### Setting and recruitment

This trial will be conducted from March 9, 2022, to March 2023 at different community centers of ten districts of Rwanda: Gasabo, Karongi, Rubavu, Rulindo, Burera, Gatsibo, Gicumbi, Nyanza, Muhanga, and Nyamagabe. The first endline survey will be done after the full cycle of fifteen weekly sociotherapy sessions whereas the second endline survey will be done 9 months after the baseline survey. The study will recruit participants through CBS facilitators based on the inclusion criteria of the trial. A total of 1200 participants who meet the eligibility criteria will voluntarily participate in the trial and will be asked to sign the informed consent form that has been approved by the ethics committee before enrolment. Participants from both rounds will be recruited in different (not neighboring) cells to minimize spillover.

### Eligibility criteria

#### Inclusion criteria

Everyone who is invited by a CBS facilitator for eventual participation is eligible. A CBS facilitator is a member of the community who has been selected and trained by CBS as an organization following criteria such as wisdom, integrity, openness, and capacity to care. The recruitment of participants in Sociotherapy is done following CBS guidelines on recruitment and involves CBS facilitators and sometimes community leaders. Basically, the recruitment is a community-based activity where CBS facilitators through word to mouth identify and visit potential participants of whom they become aware that they could potentially benefit from psychosocial support offered through CBS.

#### Exclusion criteria

Those who have gone through CBS in previous projects will not be eligible.

### Ethical issues

Ethical approval has been granted by the Institutional Review Board of the College of Medicine and Health Sciences at the University of Rwanda. The trial has been registered with ISRCTN (ISRCTN11199072, registered on April 2, 2022). Eligible participants will be informed about this trial and sign the consent forms before participating in the study. The trained data collectors will obtain informed consent from trial participants invited by the CBS facilitators. To comply with ethical considerations, participants assigned to a waiting list (control groups) will participate in the intervention after the final evaluation exercise (nine months later). All data collected for the purpose of this study will remain confidential and accessible only to the research team. All information will be stored in a password-protected computer.

### Randomization

University of Rwanda (UR) researchers, who are performing an external evaluation, will randomly select 80 groups from the CBS organization list of 137 groups. After baseline data collection from 80 groups, the computer-generated randomization sequence numbers will be generated using the SPSS (Version 28.0) statistical software. This indicates that 57 groups will be excluded from the study. The UR researchers will randomly assign the groups of participants (i.e., clusters) to either the intervention or control arms, observing a 1:1 ratio. The two rounds of endline data will be collected immediately after the 15-week intervention and 9 months post-intervention. At the baseline, the data collectors and study participants will be blinded. At endline, we will use the same blinding communication strategy. However, in reality, we do not expect the data collectors and study participants to be blinded anymore, as study participants become easily aware of which group they belong to, and they typically share this information with each other. In our experience implementing comparable RCT research, despite our efforts to create believable placebo intervention for the control group and despite dedicated efforts to blind data collectors and participants, we have observed that blinding in reality did not work.

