### Sample size

The sample size was estimated based on pilot study results. As there was no similar previous study allowing to asses intraclass correlation, the authors of this study have conducted a pilot study on a sample of 559 people. The objectives of the pilot study were (1) to test the psychometric properties of the Social Dignity Scale and (2) to assess potential Intra-CBS groups correlation. The results from the pilot study revealed an intraclass correlation of 0.15. The targeted treatment effects were established in terms of clinical judgment, not through the pilot of data [37]. According to previous CBS experience, an average of 3 out of 15 participants in a CBS group dropout the intervention without achieving at least 11/15 required sessions. All enrolled CBS groups are facilitated to the end of the intervention. Considering an intraclass correlation coefficient, Rho = 0.15 and a standard Alpha = 0.05, an a priori power calculation using the Optimal Design Software [38] revealed that 80 CBS groups (40 control and 40 intervention) composed of 12 participants each group would make it possible to achieve the standard power of 0.80 while detecting a small Cohen’s *d* effect size of 0.3. The required total sample was then found to be 960 (i.e., 12 × 80) participants. However, assuming a minimalistic response rate of 96% according to a previous similar social study in Rwanda evidencing that it ranges from 96% [39] to 99.8% [40], we would need to recruit 1000 participants. To provide a buffer against potential attrition-related problems, at least 15 recruited beneficiaries of CBS that fulfil the inclusion criteria will be included in the study making the final sample size to recruit up to 1200 participants.

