### Assignment of interventions: allocation

#### Sequence generation

The computer-generated randomization sequence numbers will be generated using the SPSS (Version 28.0) statistical software. Details of the procedure are described in the “Randomization” section.

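### No district stratification is stated for the 1:1 allocation of 80 groups across ten districts, which forgoes precision if districts differ; how the non-neighbouring-cell rule is applied also needs stating

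*Protocol article*

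**What the plan says.** The Setting and recruitment section places the trial "at different community centers of ten districts of Rwanda". Under Randomization, the university researchers "will randomly select 80 groups from the CBS organization list of 137 groups". The order of steps is then fixed: "After baseline data collection from 80 groups, the computer-generated randomization sequence numbers will be generated using the SPSS (Version 28.0) statistical software". The researchers "will randomly assign the groups of participants (i.e., clusters) to either the intervention or control arms, observing a 1:1 ratio". The Sequence generation section adds no restriction and refers back: "Details of the procedure are described in the “Randomization” section".

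The Baseline characteristics section lists group location among the cluster-level variables to be tabulated by arm as a check on balance. The Primary analysis section models change in social dignity with the baseline score as a control and adjusts for pre-defined covariates that it does not name.

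On contamination, Setting and recruitment states: "Participants from both rounds will be recruited in different (not neighboring) cells to minimize spillover". It does not say what the two rounds are. The Randomization section does not mention cells.

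**The concern.** The only rule stated for allocation is the 1:1 ratio. District is available when the sequence is generated, and the plan cares enough about location to tabulate it by arm, but only after arms are fixed. With ten districts and 80 groups, allocation with no other rule will usually leave some districts clearly lopsided. Between-group variance is the larger part of the standard error here ("The results from the pilot study revealed an intraclass correlation of 0.15"), so any share of it that belongs to district could be removed by stratifying and modelling district. At stake is a modest amount of power in a design planned with almost none to spare.

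The second matter is one of clarity. Arms are assigned after groups have been formed and measured at baseline, so recruiters cannot separate intervention from control groups by arm. The cell rule can therefore keep the arms apart in only two ways: the groups are mutually non-neighbouring whatever their arm, or a later step enforces the separation. The article does not say which applies.

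**Working it through.** **Inputs from the Sample size section:** ICC 0.15; alpha 0.05 (sidedness not stated, two-sided assumed); 40 + 40 groups of 12; d = 0.3; power 0.80. **From Setting and recruitment:** ten districts. **Assumed, because the documents do not give them:** 8 groups per district (80/10), and the share *s* of between-group variance that lies between districts.

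**1. The plan's own figure.** The design effect is 1 + (12 − 1) × 0.15 = 2.65. In standardised units

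SE = √[(4/80) × (0.15 + 0.85/12)] = √(0.05 × 0.2208) = 0.105.

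The noncentrality is 0.3/0.105 = 2.855. The noncentral t on 78 df gives power 0.805, and the normal approximation gives 0.815. The stated 0.80 is reproduced, and the calculation contains no district term.

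**2. Chance imbalance when 1:1 is the only rule.** With 40 of 80 groups allocated to intervention and 8 groups in a district, the number of intervention groups in that district is hypergeometric.

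- P(6:2 or worse) = 2 × 0.1317 = 0.263, so 10 × 0.263 = 2.6 districts are expected to be that uneven.
- By simulation, at least one of the ten is 6:2 or worse with probability 0.94, and at least one is 7:1 or worse with probability 0.43.
- On average 2.9 of the ten split exactly 4:4.

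**3. What stratifying and modelling district could return.** District takes 9 df, leaving 78 − 9 = 69, and

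SE(s) = √[(4/80) × (0.15(1 − s) + 0.85/12)].

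| District share *s* (assumed) | SE | Power at d = 0.3, 69 df |
|---|---|---|
| 0% | 0.105 | 0.804 |
| 10% | 0.101 | 0.830 |
| 20% | 0.098 | 0.857 |
| 30% | 0.094 | 0.884 |
| 50% | 0.085 | 0.934 |

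The first row is the worst case: 0.804 against 0.805 without stratification.

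**4. A limit on step 3.** These figures treat the outcome as an unadjusted score with ICC 0.15. The primary analysis uses change with the baseline score in the model, which would already remove part of any stable difference between districts. The gain would then be smaller than in the table. The documents give no ICC for the adjusted outcome, so the reduction cannot be computed.

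**5. The cell rule against the allocation steps.** Setting and recruitment places the rule at recruitment and attaches it to two rounds. The only rounds mentioned under Randomization are the two endline data collections, which does not fit a rule about where people are recruited. If every listed group is in a cell that adjoins no other listed group's cell, any draw of 80 and any allocation satisfies the rule. If not, two drawn groups in adjoining cells would fall in opposite arms with probability 40/79 = 0.51. The number of such pairs is not given and may be zero.

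**The case against.** **Silence is not a statement.** The article never calls the allocation simple or unstratified, and it condenses a fuller protocol. This stands in part. However, the Sequence generation section names the Randomization section as the place for the details, and the only constraint there is the ratio. The fair wording is that no stratification is stated.

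**The plan meets its own target.** This stands. The 0.80 power holds for unstratified allocation, and such allocation does not bias the estimate. A reader might infer that the trial is underpowered or loses precision as planned. The documents do not support that: this is a gain not taken, its size rests on a district share that they do not give, and it is nil if districts do not differ.

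**Adjustment may recover some of it.** This also stands in part. Baseline adjustment shrinks the gain, and location may be among the pre-defined covariates. Because those are not named in the article, adjustment for district cannot be taken as assured.

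**Spillover is handled at recruitment.** A reader might infer that neighbouring intervention and control groups are left to chance and that the effect will be diluted. The documents do not show this. The rule is placed at recruitment, and the list of 137 may already satisfy it. What remains is that the rounds are undefined and the step at which the rule operates is not stated.

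**Conclusion.** The point holds as a recommended design improvement. No use of district in allocation is stated, although district is known beforehand, and material imbalance in some districts is likely (probability 0.26 of 6:2 or worse for a given district, assuming 8 groups in each). Stratifying by district and modelling it would raise power by about 2.5 or 5 percentage points if district carries 10% or 20% of the between-group variance, and by less after baseline adjustment. At worst it costs about 0.001 of power. It corrects neither a bias nor a shortfall against the stated 0.80.

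On spillover, the supportable conclusion is only that Setting and recruitment and Randomization need to be reconciled. No failure of the cell rule is established.

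**What to change.** 1. Before allocation, randomise groups 1:1 within district using permuted blocks, and say so under Randomization. Where a district has an odd number of drawn groups, allocate the leftover groups together so that the total stays 40:40.
2. Name district as a term in the primary model. If allocation has already taken place, this step alone would still recover part of the gain.
3. In Setting and recruitment, define the two rounds. State whether the 137 listed groups are already in non-neighbouring cells or whether the draw of 80 enforces this.

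The first two changes take a few lines in the randomisation program, one model term and about 9 df. The third takes a sentence or two if the list has already been screened. If the draw must enforce the rule, someone must first check that 80 mutually non-adjoining groups exist among the 137, which the documents do not show. Allocating adjoining cells to one arm as a single unit is not recommended here without a stated power cost, because it would reduce the number of independently randomised units below 80.

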### The intervention

#### Explanation for the choice of comparators

In this trial, the intervention groups will receive CBS whereas the control group will be on a waiting list to estimate the relative effect of CBS on social dignity and the secondary outcomes. To comply with ethical considerations, participants assigned to a waiting list (control groups) will also participate in the intervention after the evaluation exercise (six months later).

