#### Provisions for post-trial care

There is no risk associated with participating in this study, except perhaps the risk of some discomfort that participants may feel as we ask questions about their personal life. Moreover, a team of clinical psychologists will provide psychological support in the intervention of emotional crises. No direct compensation will be allocated to participants. Participants in the control group are waitlisted and will be invited to join CBS groups in future post-study intervention cycles.

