#### Primary analysis

The primary analysis will be performed following an intention-to-treat analysis. Primary outcome measures will be the post-intervention continuous total score of the social dignity questionnaire and its subscales based on socio-therapy phases. As the researchers are interested in discussing change and the correlates of change [42], the primary analysis will compare intervention vs control groups on their mean change in social dignity between baseline and endline, and between baseline and endline2 separately. To counter the problems associated with their use, the baseline scores will be incorporated into the model as a control [42, 43]. The mean change scores in social dignity will be incorporated into the GEE model as a dependent outcome. GEE will help to adequately account for intra-cluster correlation by incorporating in the model the random CBS groups/cluster-specific effect. Our primary interest is at the individual level and the CBS groups/cluster level will be regarded as a nuisance that must be considered for valid inferences [44].

Allocated groups (control versus intervention) will be regarded as fixed effects while clusters and time points are regarded as random effects in the model. With this approach, we will be able to separately model the mean response at the individual level and the cluster within-cluster association. The model will be adjusted using pre-defined covariates. Our primary interest is at the individual level, and the cluster level is regarded as a nuisance that must be considered for valid inference. We will test the robustness of the results by repeating the analyses using mixed random effects regression analysis to compare the two groups and a standard *t*-test to compare the means of the outcomes at the individual level [45, 46]. The estimated difference in mean change from baseline to endline and the corresponding 95% confidence interval (CI) will be presented. Secondary outcomes will be analyzed using the same method as the primary outcome.

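### Control release and endline 2 are each timed in two ways, so the endline 2 primary comparison is not securely CBS versus no CBS

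*Protocol article*

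**What the plan says.** Three sections of the protocol article speak to when controls receive CBS:

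- Explanation for the choice of comparators: "participants assigned to a waiting list (control groups) will also participate in the intervention after the evaluation exercise (six months later".
- Ethical issues: controls "will participate in the intervention after the final evaluation exercise (nine months later".
- Provisions for post-trial care: "Participants in the control group are waitlisted and will be invited to join CBS groups in future post-study intervention cycles".

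The first two give different intervals, and neither says from which event the months are counted. The first also does not say which evaluation is meant.

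Two sections date the second endline survey:

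- Setting and recruitment: "the second endline survey will be done 9 months after the baseline survey".
- Randomization: "The two rounds of endline data will be collected immediately after the 15-week intervention and 9 months post-intervention".

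The Primary analysis section compares the arms on "mean change in social dignity between baseline and endline, and between baseline and endline2 separately", so endline 2 carries one of the two primary comparisons. The section on usual care describes the contrast as people who received CBS against eligible people who were placed on the waiting list.

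**The concern.** The endline 2 comparison estimates a lasting effect of CBS against no CBS only if controls have not begun CBS when they are surveyed. That depends on the order of two events, release and survey, and the protocol gives two figures for each. If staff took the release interval from one section and the survey date from another, controls could be part-way through CBS or finished with it at endline 2. The analysis would then compare earlier with later CBS, and a benefit that lasts could show up as a small difference or none. Once controls have started CBS, the untreated comparison at that time point cannot be recovered.

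**Working it through.** **Inputs from the protocol.** CBS runs for 15 weekly sessions (Setting and recruitment). Release is at six or nine months, and endline 2 is nine months after baseline or nine months post-intervention, as quoted above. ICC 0.15, alpha 0.05, 80 groups (40:40), 12 per group, d = 0.3, power 0.80 (Sample size).

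**Assumptions.** CBS starts at baseline (month 0); the test is two-sided.

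**1. The plan's own sample size.**

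SE = sqrt[(4/80) × (0.15 + 0.85/12)] = sqrt(0.05 × 0.2208) = 0.105.

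Non-centrality = 0.3/0.105 = 2.86. With a non-central t on 78 df, power is 0.805, which agrees with the stated 0.80. The smallest even number of groups reaching 80% power is 80, hence 80 × 12 = 960. Then 960/0.96 = 1000 and 15 × 80 = 1200. All the stated figures reproduce.

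**2. The two dates for endline 2.**

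Length of CBS = 15 × 7/30.44 = 3.45 months. Endline 2 is therefore at month 9.0 (Setting and recruitment) or month 9 + 3.45 = 12.45 (Randomization). The gap is about one full CBS cycle.

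**3. Release against endline 2.**

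| Release interval, counted from | Release (month) | Endline 2 at 9.0 | Endline 2 at 12.45 |
|---|---|---|---|
| Six months, baseline | 6.0 | 3.0 before | 6.45 before |
| Nine months, baseline | 9.0 | same time | 3.45 before |
| Six months, end of CBS | 9.45 | 0.45 after | 3.0 before |
| Nine months, end of CBS | 12.45 | 3.45 after | same time |

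Release precedes endline 2 in 3 of 4 pairings counted from baseline and in 1 of 4 counted from the end of CBS, so in 4 of 8 overall. If intervals counted from endline 2 itself are added, release is always later and the count is 4 of 12.

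In the four early pairings the lead is 3.0, 3.0, 3.45 or 6.45 months. A lead of 3.0 months is 3.0/3.45 = 87% of a cycle; the other two allow a complete cycle.

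**4. Endline 1.** It falls at about month 3.45. The earliest release in the table is month 6.0, so endline 1 precedes release throughout.

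**5. Illustration of the loss at endline 2.** Suppose controls have gained a fraction f of the effect. The expected contrast is 0.3 × (1 − f), with the same SE:

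| f | Expected contrast | Power |
|---|---|---|
| 0 | 0.300 | 0.81 |
| 0.25 | 0.225 | 0.56 |
| 0.50 | 0.150 | 0.29 |
| 0.75 | 0.075 | 0.11 |
| 1 | 0 | 0.05 |

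The protocol gives no value for f; the range is shown because the true figure is unknown.

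**The case against.** The strongest reply is that the protocol states the order even where its month counts disagree. Ethical issues puts release after the final evaluation, Provisions for post-trial care puts it after the study, and no section says that controls receive CBS before endline 2. Four of the five sections can also be made to agree. Six months counted from the end of CBS is month 9.45, close to nine months after baseline, and only the Randomization section then stands apart. The schedule figure and study-schedule table are not reproduced in the text reviewed and may settle the dates.

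Much of this stands. A reader might infer from the conflicting intervals that controls will, on most readings, already have been treated at endline 2. The documents do not support that. The 3-of-4 majority exists only if every release interval runs from baseline, which neither release passage says. Across the two starting points it is half, and the ordering words point the other way. In two of the four early pairings controls would be late in CBS, not finished. A reader might also expect a reversed effect at endline 2; that needs an assumed fading of benefit for which the protocol gives no figure.

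The reply does not remove the conflict. The four-section reading has to supply starting points that the text omits, and the Randomization date still contradicts it. The calendar does not settle the matter either. From a baseline on 9 March 2022 both endline 2 dates fall by March 2023. From the July to August 2022 recruitment given under Trial status, nine months after baseline already runs from 31 March to 31 May 2023.

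**Conclusion.** The point holds in limited form. Release of controls and the date of endline 2 are each given two ways in the current text, and the two endline 2 dates lie 3.45 months apart. The intended order appears to be survey first. The stated intervals do not secure it, because 4 of the 8 pairings counted from baseline or the end of CBS would have controls in or past CBS at endline 2. The endline 2 primary comparison is therefore not securely CBS versus no CBS. Endline 1, the other primary comparison, is unaffected.

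The timeline arithmetic assumes that CBS begins at baseline. The power figures further assume that release does come first and that controls gain a given fraction of d = 0.3; they show sensitivity and predict nothing. The documents do not show which interval is intended.

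**What to change.** Reconcile Setting and recruitment, Ethical issues, Randomization, Explanation for the choice of comparators, and Provisions for post-trial care into one timeline. The length of the wait is for the sponsor and the ethics committee to set. Define endline 2 by a single interval from one starting point common to both arms. Record, for each control group, the date of its endline 2 survey and the date of its first CBS session.

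Add a reporting rule to Primary analysis. All randomised groups stay in the intention-to-treat analysis at endline 2. The result is reported as CBS versus waitlist only if controls were surveyed before release. Otherwise it is reported as earlier versus later CBS, with endline 1 as the only comparison against untreated controls. This is a rule about labelling and should not be used to drop groups.

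The cost is a few corrected sentences, two dates per control group and one analysis rule, with no extra participants. The downside is a narrower endline 2 claim if controls are released first.
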